## Treatments Potentially Interfering with Vaccine-Induced Immunity

**The following criteria should be checked at each visit. If any become applicable during the study, the subject will not be required to discontinue, but a separate analysis may be done which excludes these individuals. See Section 13.3 for definitions of study cohorts and data sets to be evaluated.**

- Use of any investigational drug or vaccine other than the study vaccine during the study period.
- Administration of chronic (defined as more than 14 days) immunosuppressants or other immune-modifying drugs within 6 months of vaccination. (For corticosteroids, this will mean prednisone, or equivalent, greater than or equal to 0.5 mg/kg/day. Inhaled and topical steroids are allowed.)
- Administration of a vaccine not foreseen by the study protocol during the period starting from 30 days prior to first dose to 30 day after the third dose visit.
- Administration of immunoglobulins or any blood products up to 30 days after the last dose of vaccine.

## Contraindications to Vaccination

**The occurrence, in any eligible study subject, of any of the events enumerated in Section 7.9.6 (“Dose Discontinuation in Individual Subjects”) represents a contra-indication to further immunization of that subject. However, the parent(s) of such a subject will be encouraged to continue participation in the safety and immunogenicity evaluation for the duration of the study.**

## Indications for Deferral of Vaccination

**The following adverse events constitute grounds for deferral of vaccine administration at a given point in time; if any one of these adverse events occurs at the time scheduled for vaccination, the subject may be vaccinated at a later date, within the allowable time interval specified in the protocol (see Section 8.2), or may be permanently discontinued from further vaccination at the discretion of the investigator (the only withdrawals from follow-up, i.e., from the study proper, would be for withdrawal of consent). The subject must be followed until resolution of the event as with any adverse event (see Section 11). If the subject is discontinued from further vaccination, the parent(s) will be encouraged to keep the subject in the safety and immunogenicity evaluation for the duration of the study.**

- Axillary temperature > 37.5 °C or evidence of clinical malaria (see Section 8.3.1) at the time of vaccination will warrant deferral of immunization until fever and symptoms resolve.
- Any other condition that in the opinion of the investigator poses a threat to the individual if immunized or that may complicate interpretation of the safety of the vaccine following immunization.

Such subjects will be followed daily in the clinic until the symptoms resolve or the window for immunization expires. No further vaccination will be performed if the subject does not recover (axillary temperature < 37.5°C or lack of symptoms, as appropriate) within 7 days of the originally scheduled vaccination date. The subject, however, will continue to be followed for safety and immunogenicity. **If the subject meets any of the above criteria for deferral on the day of first immunization the PI may elect to exclude the subject from further participation in the study.**

## Safety Plan

### **Definitions**

“Discontinuation of vaccination” is the temporary or permanent withholding of further vaccinations from all or some study groups in the trial.

“Dose escalation” refers to the decision to progress from 1/5 dose to ½ dose or from ½ dose to full dose. This progression is from one cohort (dose level) to another.

“Administration of consecutive doses” refers to the progression from the 1st dose to the 2nd dose, and from the 2nd dose to the 3rd dose. This progression is from one monthly inoculation to the next in the subjects of a given cohort.

“Dose limiting toxicities” refer to AEs that preclude further dose escalation or administration of consecutive doses.

### **7.9.2 Criteria for Discontinuation of Vaccination**

If any of the following SAEs occur, discontinuation of vaccination will be invoked and the events will be reported as described in Section 11.5.

1. Death in any subject in which the cause of death is judged to be possibly, probably or definitely related to study vaccine
2. The occurrence in any subject of an anaphylactic reaction to study vaccine
3. The occurrence in any subject of a life-threatening SAE whose causal relationship to vaccination is judged to be probable or definite
4. The occurrence of one or more non-life-threatening SAEs whose causal relationship to vaccination is judged to be definite
5. The occurrence, in one or more subjects, of Grade 4 laboratory abnormalities (See Table 5, “General Toxicity Table”), judged to be probably or definitely related to receipt of study vaccine

The following dose limiting toxicities will preclude dose escalation to the next higher dose level or administration of consecutive doses within a dose level (See Table 5):

1. In 4 (10%) or more children within a cohort, occurrence of Grade 3 or greater solicited systemic (not local) AEs judged probably or definitely related to the study vaccine, , , or
2. In 4 (10%) or more children within a cohort, occurrence of Grade 2 or greater unsolicited AEs judged probably or definitely related to the study vaccine, or
3. In 4 (10%) or more children within a cohort, occurrence of laboratory studies indicating Grade 2 or greater toxicities that are judged to be probably or definitely related to the study vaccine.

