RAP: Reporting and Analysis Plan

RIA Radioimmunoassay

RR: Relative risk

RTS,S: A candidate malaria vaccine antigen [See next 2 entries]

RTS: Fusion protein consisting of a circumsporozoite protein-based antigen and HBsAg

S: 226 amino acid polypeptide corresponding to the surface antigen of hepatitis B virus (adw serotype)

SAE: Serious adverse event

SB Biologicals/SB Bio: SmithKline Beecham Biologicals

SB62: An oil in water emulsion

SBAS2: SmithKline Beecham Adjuvant System 2

SCI: Statistics Collaborative, Inc

Sf9 Insect cells derived from *Spodoptera frugiperda* (army

worm)

SI: *Systemè* *International* [*d’Unité*]; International System [of

Units]

SID: Subject identification (number or card)

SOP: Standard Operating Procedure

SPP: Study Specific Protocol

SQ: Subcutaneous; subcutaneously

SU: Suspected

TRAP: Thrombospondin-related anonymous protein

UL: Unlikely to be related

USAID: US Agency for International Development

USAMMDA: US Army Medical Materiel Development Activity

USAMRMC: US Army Medical Research and Materiel Command

Vacc: Vaccination

WB: Western Blot assay

WRAIR: Walter Reed Army Institute of Research, Silver Spring,

MD, USA

WRAMC: Walter Reed Army Medical Center, Washington, DC, USA

WRP: Walter Reed Project (WRAIR in Kenya)

WRP KC: WRP Kombewa Clinic

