### **7.9.3 Safety Review Prior to Dose Escalation**

Following the 7 day period after immunization (and prior to a dose escalation) the LMM will review all available information regarding solicited and unsolicited AEs and SAEs. As there are 6 dose escalations (Doses 1b, 1c, 2b, 2c, 3b, and 3c), there will be 6 such reviews by the LMM. (See Section 8.1.2: ‘Vaccination Process’ and Appendix B [Section 17.2.5: ‘Specific Schedule of Events’]).

Dose escalation will not proceed until all of the following four events have occurred:

1. All study subjects in a given cohort (dose level) have received an injection of study vaccine, and
2. All such subjects have been followed for at least 7 days after the injection, and
3. The LMM has reviewed the available safety data (and has had the opportunity to discuss the data with the DSMB, if he feels it necessary), and recommends further dose escalation and
4. The PI has determined that none of the SAEs or dose limiting toxicities outlined in Section 7.9.2 have occurred.

An additional requirement obtains prior to the first two dose escalations (i.e., prior to Doses 1b and 1c, during the first month of injections). This is a requirement that the DSMB will also review the LMM safety data report (number 3 above) and must concur on the decision to dose escalate, and convey this directive to the PI in writing. For these first two dose escalations, therefore, concurrence to proceed must be forthcoming from both the LMM and the DSMB. Courtesy copies of these reports will also be sent to GSK Biologicals, MVI and SCI. The DSMB is not required to respond to data reports prior to subsequent dose escalations (Doses 2b, 2c, 3b or 3c), although it may do so at its own discretion.

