### **7.9.6 Dose Discontinuation in Individual Subjects**

Reasons for discontinuation of study vaccine administration in an individual subject include, but are not limited to, the following:

1. Anaphylactic reaction following administration of study vaccine
2. Significant (Grade 3 or 4) reactions following administration of study vaccine (including severe pain, severe swelling, severe headache, persistent high fever or other severe systemic or local reactions) that, in the opinion of the investigator or sponsor, preclude further administration of study vaccine
3. The occurrence of an SAE (See Section 11.5.1) whose relationship to the study vaccine is judged to be possible or probable
4. Receipt of any investigative drug, investigative vaccine or immunosuppressive medication (inhaled or topical corticosteroids are allowed) within 28 days of study vaccine
5. The occurrence of other medical conditions, unrelated to study vaccine, which, in the opinion of the PI, contraindicate administration of study vaccine
6. Moderate or severe unsolicited AEs (clinical events or laboratory tests) that are indicative of new and significant end organ dysfunction

**Table 5: General Toxicity Table** (Modified from the Pediatric ACTG Toxicity Tables; See Ref. 43)

| **Event** | **Grade I** | | **Grade 2** | | **Grade 3** | | | **Grade 4** | |
| --- | --- | --- | --- | --- | --- | --- | --- | --- | --- |
| **Laboratory Values** | | | | | | | | | |
|  | Conventional  Units | SI Units | Conventional Units | SI Units | Conventional Units | SI Units | | Conventional Units | SI Units |
| Hemoglobin | 7.0-7.9 gm/dL | 4.4-4.9 mmol/L | 6.0-6.9 gm/dL | 3.8-4.39 mmol/L | <6.0 gm/dL | <3.8 mmol/L | | CHF 2o to anemia | CHF 2o to anemia |
| Leukocytes | 3.0-3.9 103  per mm3 | 3.0-3.9 109/L | 2.0-2.9 103  per mm3 | 2.9-2.0 109/L | 1.0-1.9 103  per mm3 | 1.9-1.0 109/L | | <1.0 103  per mm3 | <1.0 109/L |
| Platelets | 90,000-109,999 per mm3 | 90.0-109.9 109/L | 75,000-89,999  per mm3 | 75.0-89.9 109/L | 50,000-74,999 per mm3 | 50.0-74.9 109/L | | <50,000 per mm3 | <50.0 109/L |
| Creatinine | 1.1-1.9 mg/dL | 92-176 mol/L | 2.0-3.9 mg/dL | 177-353 mol/L | 4.0-5.9 mg/dL | 354-530 mol/L | | >6.0 mg/dL | >530 mol/L |
| ALT | 45-60 IU/l | 45-60 IU/l | 61-105 IU/l | 61-105 IU/l | 106-147 IU/l | 106-147 IU/l | | > 148 IU/l | > 148 IU/l |
| **Systemic Events** | | | | | | | | | |
| Fever | 37.5-38.0oC | | 38.1-39.0oC | | 39.1-40.5oC | | >40.5o persistent >48 hours | | |

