### **Solicited Adverse Events**

**Table 12. Solicited Adverse Event (AE) Categories**

| Categories | Adverse Events |
| --- | --- |
| Local (injection site) AEs | Pain at the injection site |
| Swelling at the injection site |
| General (systemic) AEs | Fever (i.e., axillary temperature  37.5°C) |
| Drowsiness |
| Loss of appetite |
| Irritability/fussiness |

N.B.: Axillary temperature will be recorded at the time of the clinic visit. Should additional temperature measurements be recorded at another time of day, the highest temperature will be recorded.

The assessment of severity/intensity will be as described in Section 11.2. For general signs and symptoms reported, the investigator should assign a causality as described in Section 11.3.

For all signs and symptoms reported, the investigator should report the outcome as described in Section 11.4.

**If an SAE (see Section 11.5) occurs at any time during the study period, the PI will inform the USAMRMC-RCQ within 24 hours by e-mail, fax or telephone and with a written report within 3 working days. The WRP/KEMRI Ethics Review Commit-tee, GSK Biologicals, HSRRB, MVI, the DSMB and the Local Medical Monitor will also receive the written report and so will also be notified within 3 working days.**

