### **Unsolicited Adverse Events**

Space will be provided in the CRF for the recording of unsolicited symptoms. Unsolicited symptoms are any AEs reported by the subjects or their parents within 30 days of a vaccination that are different from those solicited symptoms recorded during the 7 day post-vaccination follow-up period. Should any general (systemic) signs or symptoms be reported, their relationship with the study vaccine will be assessed by the investigator and transcribed into the CRF, as described in Section 11.3.

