## Assessment of Causality

Every effort will be made by the investigator to explain each AE and determine its causal relationship, if any, to administration of the study vaccine.

The degree of certainty with which an AE can be attributed to administration of the study vaccine (or alternative causes, e.g., natural history of underlying diseases, concurrent therapy, etc.) will be determined by how well the event can be understood in terms of one or more of the following:

- Reactions of a similar nature having previously been observed with this type of vaccine or formulation.
- The event having often been reported in literature for similar types of vaccines.
- The event being temporally associated with vaccination or reproduced on re-vaccination.

All solicited local (injection site) reactions will be considered causally related to vaccination.

Assessment of causality in all other AEs should be documented by the investigator by answering the following query on the “Serious and Unexpected Adverse Event Report”:

In your opinion, did the vaccine(s) possibly contribute to the adverse event?

NO; Either the adverse event is not causally related to administration of the study vaccine or

there are other, more likely causes and administration of the study vaccine is not suspected

to have contributed to the adverse event.

YES; There is a reasonable possibility that the vaccine contributed to the adverse event.

Non-serious and serious AEs will be evaluated as two distinct events given their different medical nature. If an event meets the criteria to be determined “serious” (see Section 11.5.1 for definition of an SAE), it will be investigated by the PI to the extent that a determination of ALL relevant contributing factors can be made.

A partial list of possible contributing factors might include:

- Past medical history
- Concurrent medications
- Protocol required procedures
- Lack of efficacy of the test vaccine
- Erroneous vaccine administration

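### The dose-limiting rules in 7.9.2 count only events of probable or definite relatedness, but the causality record prescribed in 11.3 is a YES/NO answer that cannot supply that count

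*Protocol*

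**What the plan says.** **The rules.** Protocol section 7.9.2 sets three dose-limiting rules, each triggered by 4 or more children within a cohort. The first concerns "occurrence of Grade 3 or greater solicited systemic (not local) AEs judged probably or definitely related to the study vaccine". The second (Grade 2+ unsolicited events) and third (Grade 2+ laboratory toxicities) use the same relatedness condition. The discontinuation criteria in that section also use graded terms: a death counts from possible upwards, a life-threatening SAE and a Grade 4 laboratory abnormality from probable upwards, and another SAE only if definite.

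**The record.** For solicited general symptoms (fever, drowsiness, loss of appetite, irritability), section 11.1.5 states: "For general signs and symptoms reported, the investigator should assign a causality as described in Section 11.3". For unsolicited general symptoms, section 11.1.6 states that "their relationship with the study vaccine will be assessed by the investigator and transcribed into the CRF, as described in Section 11.3". Section 11.3 treats solicited local reactions as related. For every other AE it documents causality by one question, "In your opinion, did the vaccine(s) possibly contribute to the adverse event", answered NO or YES. YES is explained as: "There is a reasonable possibility that the vaccine contributed to the adverse event".

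**Who applies the rule.** Before each escalation, section 7.9.3 requires as its fourth condition: "The PI has determined that none of the SAEs or dose limiting toxicities outlined in Section 7.9.2 have occurred". Section 7.9.4 repeats this for consecutive doses.

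**Other vocabularies.** Section 7.9.6 stops dosing in a child for an SAE "whose relationship to the study vaccine is judged to be possible or probable". The List of Abbreviations carries NR, SU and PB, and "UL: Unlikely to be related", with no entry for definite. The body of the protocol does not use these codes.

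**The concern.** The rule needs a finer causality grade than the protocol tells staff to record. Both sides are fixed in this document, so this is not a detail left to an analysis plan.

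Rule 1 is the only numeric limit on solicited systemic reactions as the dose rises from 10 to 25 to 50 µg in children aged 12 to 47 months. If 4 or more children in a cohort have a qualifying YES event, one reader can say the limit is reached and another that it is not, from the same record and without either departing from the protocol. Nobody checking the file later could tell which was right.

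Section 11.3 also places its question on a report for serious and unexpected events, although a Grade 3 fever need be neither.

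**Working it through.** **1. The plan's own threshold.** Section 7.2 gives 45 children per cohort (30 FMP-1, 15 rabies vaccine). 10% of 45 = 4.5, and 4/45 = 8.9%. The stated trigger of 4, labelled 10%, is consistent within rounding and is not in dispute.

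**2. Can the rule's count be obtained from the prescribed answers?**

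| Needed by | Relatedness required | Available from 11.3 |
|---|---|---|
| 7.9.2, three 4-child rules | probable or definite | YES or NO |
| 7.9.2, life-threatening SAE; Grade 4 laboratory | probable or definite | YES or NO |
| 7.9.2, other SAE | definite | YES or NO |
| 7.9.2, death | possible or above | YES comes close to this |
| 7.9.6, SAE in one child | possible or probable | YES or NO |

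Laboratory abnormalities belong here because the AE definition in 11.1.1 includes them and the 11.3 question covers all AEs other than solicited local reactions. No section maps YES to probable or definite.

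Let Y be the number of children with a qualifying YES event, and R the number whose event is probable or definite. All that follows is 0 ≤ R ≤ Y.

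- Y ≤ 3: R ≤ 3, so the rule is not met.
- Y ≥ 4: R may lie on either side of 4, and the record does not say which.

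**3. How much the reading can matter (illustration).** Two inputs are assumptions, not protocol figures:

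- q = chance that a child has a Grade 3+ systemic event answered YES in the review window;
- f = share of those that would be held probable or definite.

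With children independent, R ~ Bin(n, q × f), and the rule trips with probability

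P(R ≥ 4) = 1 − Σ(k = 0 to 3) C(n, k) (qf)^k (1 − qf)^(n−k).

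For n = 45 and q = 10%, the expected counts are 45 × 0.10 × f = 4.5, 2.25 and 1.125 at f = 1, ½ and ¼. The probabilities are:

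| n | q | f = 1 (every YES counts) | f = ½ | f = ¼ |
|---|---|---|---|---|
| 45 | 5% | 18.7% | 2.6% | 0.2% |
| 45 | 10% | 67.1% | 18.7% | 2.6% |
| 45 | 15% | 92.2% | 43.9% | 8.8% |
| 30 (FMP-1 recipients only) | 10% | 35.3% | 6.1% | 0.6% |

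The f = 1 column is also the probability that Y reaches 4, that is, that the ambiguity arises at all. At low event rates it seldom does.

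**The case against.** **Section 11.3 does ask for judgement.** Before its question it says that the degree of certainty of attribution depends on similar reactions seen before, the literature, timing and recurrence. That gives a basis for grading, and the PI can grade relatedness on it. It sets no boundary between possible, probable and definite, and the answer to be documented is still YES or NO.

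**The CRF may hold a graded scale.** Section 11.1.3 requires the relationship to vaccination to be established on the Adverse Event Form without limiting it to YES/NO, and the abbreviation codes could be traces of such a scale. The form is not in the document, so this cannot be excluded. Even so, the protocol names the YES/NO question as the method, and the listed codes lack the definite category that 7.9.2 needs.

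**Other safeguards.** A reader might infer that the LMM and DSMB have no means of checking the PI's determination, or that escalation hangs on this rule alone. The documents do not support that. Under 7.9.4 reviewers receive all AEs of the 7-day window and can count Grade 3+ children regardless of causality; fewer than 4 verifies that rule 1 is not met. The LMM must recommend each step, the DSMB must concur in writing before Doses 1b and 1c, and 11.5.2 halts all vaccination for any SAE merely suspected of being related. These protections stand, but they do not make the rule evaluable at 4 or more.

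**Malaria fever.** A reader might also infer, from the 83% parasite prevalence in section 4.8, that smear-positive fevers would disable the rule. That figure comes from a community cohort, not from trial children screened as healthy with vaccination deferred for clinical malaria. A clinician using a fully defined scale could still grade such a fever as only possible. How to attribute these fevers is a separate clinical question.

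**Conclusion.** The point holds as an inconsistency within the protocol. The three 4-child rules, and most of the SAE and Grade 4 laboratory criteria in 7.9.2, depend on a grade that 11.3 does not produce, and 7.9.6 uses a third wording. Once 4 or more children in a cohort have a qualifying YES event, the prescribed record cannot settle whether the rule is met. Below 4 there is no ambiguity.

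On the illustrative 10% YES rate in 45 children, the chance that the rule trips is 67%, 19% or 3% according to whether all, half or a quarter of the YES answers count. These figures rest on assumed q and f and on independence between children. They show that the reading can change the outcome several-fold; they do not predict how often it will.

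The correction should be made before the first dose. It concerns whether a written stopping rule can be evaluated and audited. It does not show that events would go unseen: they are still graded, reported and analysed as endpoints.

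**What to change.** 1. In 11.3, replace YES/NO with one scale (not related, possible, probable, definite) and define each grade, using the criteria already listed there.
2. Use the same words in 7.9.2 and 7.9.6, and bring the abbreviation list into line.
3. Record the grade on the Adverse Event Form for every solicited systemic AE, unsolicited AE and laboratory abnormality, not only on the serious-event report.
4. In each existing 7-day report, show the number of children with qualifying events at each causality grade, so that the LMM and DSMB can check the PI's determination directly.

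Rewording 7.9.2 to count every YES would be shorter, but it would turn a probable-or-definite rule into a possible-or-above rule (the f = 1 column), which is a different and stricter limit.

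**Cost:** a paragraph in 11.3, matching words elsewhere, one CRF field, one table in reports already planned, and short staff training. No added visits, blood or children, and the threshold of 4 is unchanged. Grading remains a clinical judgement, but a defined and recorded one.

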**Day 7  3 days Day 7 Post-vaccination 1 follow-up visit**

***Visit 6***

- Record vital signs (temperature, blood pressure, pulse)
- Examine site of injection
- Record solicited and unsolicited AEs (of previous 4 days)
- Complete physical examination
- Check concomitant medications

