**Days 14  3 days Day 14 Post vaccination 1 follow-up visit**

***Visit 7***

- Record vital signs (temperature, blood pressure, pulse)
- Brief medical history
- History-directed physical examination
- Record any unsolicited adverse events occurring after the last vaccine dose.
- Check weight
- Check concomitant medications
- Collect 2 ml of blood for determination of:
- Serum for anti-MSP-1 antibodies (Store at  -50°C)
- CBC, creatinine, ALT

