### **Specific Daily Schedule of Events**

The dates on this schedule are for planning purposes and are provisional only. This sche-dule presupposes that Cohorts B and C will be available for vaccinations two weeks after previous doses are given. Any of these vaccination dates may change to somewhat later dates, however, in the event of a temporary discontinuation of vaccinations (postpone-ment may be for up to 5 weeks) or for other unforeseen reasons.

| **Study Day** | **Date**  **(2003)** | **Cohort A** | **Cohort B** | **Cohort C** | **Events** |
| --- | --- | --- | --- | --- | --- |
| -30/31 | 27-28 MAR | Visit 0 | Visit 0 | Visit 0 | Video & Consenting for Parents |
| -5/6 | 22-23 APR | Visit 1 | Visit 1 | Visit 1 | 1st Visits & Screenings of all Subjects |
| -3/4 | 24-25 APR |  |  |  | Notifications of Enrollment |
| -2 | 26 APR |  |  |  |  |
| -1 | 27 APR |  |  |  |  |
| 0 | 28 APR | Dose 1a  Visit 2 |  |  | Enrollment & 1st Vaccination of Cohort A |
| 1 | 29 APR | Visit 3 |  |  | Post-vaccination F/U visit for Cohort A |
| 2 | 30 APR | Visit 4 |  |  | Post-vaccination F/U visit for Cohort A |
| 3 | 01 MAY | Visit 5 |  |  | Post-vaccination F/U visit for Cohort A |
| 4 | 02 MAY |  |  |  |  |
| 5 | 03 MAY |  |  |  |  |
| 6 | 04 MAY |  |  |  |  |
| 7 | 05 MAY | Visit 6 |  |  | Day 7 post-vaccination F/U visit for Cohort A |
| 8 | 06 MAY |  |  |  | Dose 1a AE Report to DSMB & LMM |
| 9 | 07 MAY |  |  |  |  |
| 10 | 08 MAY |  |  |  |  |
| 11 | 09 MAY |  |  |  |  |
| 12 | 10 MAY |  |  |  |  |
| 13 | 11 MAY |  |  |  |  |
| 14 | 12 MAY |  | Dose 1b  Visit 2 |  | Enrollment & 1st Vaccination of Cohort B  (Requirement: Formal DSMB/LMM concurrence) |
| 15 | 13 MAY | Visit 7 | Visit 3 |  | Day 15 post-vaccination F/U visit for Cohort A; Post-vaccination F/U visit for Cohort B |
| 16 | 14 MAY |  | Visit 4 |  | Post-vaccination F/U visit for Cohort B |
| 17 | 15 MAY |  | Visit 5 |  | Post-vaccination F/U visit for Cohort B |
| 18 | 16 MAY |  |  |  |  |
| 19 | 17 MAY |  |  |  |  |
| 20 | 18 MAY |  |  |  |  |
| 21 | 19 MAY |  | Visit 6 |  | Day 7 post-vaccination F/U visit for Cohort B |
| 22 | 20 MAY |  |  |  | Dose 1b AE Report to DSMB & LMM |
| 23 | 21 MAY |  |  |  |  |
| 24 | 22 MAY |  |  |  |  |
| 25 | 23 MAY |  |  |  |  |
| 26 | 24 MAY |  |  |  |  |
| 27 | 25 MAY |  |  |  |  |
| 28 | 26 MAY |  | Visit 7 | Dose 1c  Visit 2 | Enrollment & 1st Vaccination of Cohort C  (Requirement: Formal DSMB/LMM concurrence)  Day 14 post-vaccination F/U visit for Cohort B |

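### As scheduled, Dose 1b precedes any post-dose laboratory result, and Dose 1c falls on the day of the first 25 µg bloods, so the laboratory criteria lack scheduled data from the cohort just dosed

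*Protocol*

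**What the plan says.** Two rules in protocol Section 7.9.2 depend on laboratory values. Dose-limiting toxicity item 3 precludes escalation, and further doses within a level, if four or more children in a cohort have "occurrence of laboratory studies indicating Grade 2 or greater toxicities that are judged to be probably or definitely related to the study vaccine". Stopping item 5 halts vaccination on "The occurrence, in one or more subjects, of Grade 4 laboratory abnormalities" judged probably or definitely related.

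Section 7.9.3 lists four conditions for every escalation. Item 2 sets the follow-up: "All such subjects have been followed for at least 7 days after the injection". Item 3 is the LMM's review of whatever safety data are available. Item 4 reads: "The PI has determined that none of the SAEs or dose limiting toxicities outlined in Section 7.9.2 have occurred". For Doses 1b and 1c only, the DSMB must also concur. Section 11.1.4 says that the reports behind those two concurrences carry solicited adverse event data as of Days 7 and 21.

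In Section 8.2 the Day 0 blood is taken before the injection. Visits 3 to 5 and Visit 6 ("Day 7 Post-vaccination 1 follow-up visit") list no blood draw. The first post-dose CBC, creatinine and ALT are at Visit 7 ("Day 14 Post vaccination 1 follow-up visit"), for which Table 8 allows 14 ± 3 days. Section 17.2.5 places the visits on calendar days, with the caveat "The dates on this schedule are for planning purposes and are provisional only".

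**The concern.** A toxicity criterion can inform an escalation only if its data exist when the decision is taken. Escalation may follow after 7 days of follow-up, but the first scheduled post-dose blood is about a week later than that. With a two-week stagger between cohorts, the blood and the next escalation land on almost the same day, and the order is left to the calendar.

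Doses 1b and 1c first expose children to 25 µg and 50 µg, with 30 FMP-1 recipients aged 12-47 months at each level. They are also the two escalations for which the protocol adds mandatory DSMB concurrence, and Section 11.1.4 treats concurrence for 1c as covering all later doses. Changes in ALT, creatinine, platelets or haemoglobin of the size graded 2 in Table 5 may cause no symptoms, so a 7-day symptom review cannot be relied on to reveal them.

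**Working it through.** No power or sample-size formula applies. The check is date arithmetic.

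**Inputs (17.2.5, Day 0 = Monday 28 April 2003).** Dose 1b is 12 May, Cohort A Visit 7 is 13 May, and Dose 1c and Cohort B Visit 7 are both 26 May. The reports to the DSMB and LMM are on 6 and 20 May. Counting from 28 April gives Days 14, 15, 28, 28, 8 and 22, which reproduces the schedule's own day numbers. The entry after Dose 1b reads "Day 15 post-vaccination F/U visit for Cohort A".

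**Lead time = escalation day − day of the first post-dose blood in the cohort just dosed.**

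| Escalation | Dose day | First post-dose blood | Lead time | Children in that cohort with a scheduled post-dose result before the dose day |
|---|---|---|---|---|
| 1b (25 µg) | 14 | 15 (Cohort A) | 14 − 15 = −1 day | 0 of 45 |
| 1c (50 µg) | 28 | 28 (Cohort B) | 28 − 28 = 0 days | 0 of 45 |

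At 1b no child in the trial has a scheduled post-dose result. At 1c Cohort A's Day 15 bloods are 28 − 15 = 13 days old, so 10 µg data exist. What is missing is any scheduled 25 µg result before that day.

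**Reports.** The scheduled bloods follow the reports by 15 − 8 = 7 days and 28 − 22 = 6 days. The earliest draws that the window permits are Day 0 + 11 = 11 and Day 14 + 11 = 25. These are still 11 − 8 = 3 and 25 − 22 = 3 days after the reports. No permitted Visit 7 date puts a result into either report.

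**Visit window.** Visit 7 may fall from dose + 11 to dose + 17, which is seven days. With escalation at dose + 14, three of those days precede it, one coincides and three follow. The window allows an earlier result but does not secure one.

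**Table 9.** It shows Cohort A's Visit 7 on Day 13 (Sunday 11 May), one day before Dose 1b. The two schedules therefore disagree on whether the bloods precede that dose. Day 13 is still 5 days after the Day 8 report.

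**Second doses.** Visit 7 precedes Dose 2a by 29 − 15 = 14 days, 2b by 42 − 28 = 14, and 2c by 56 − 42 = 14. The laboratory criteria have scheduled data for these. At later escalations the blood taken after the latest dose is again close to or after the escalation day, but each cohort by then has bloods from earlier doses.

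**The case against.** The strongest reply is that the binding text already contains a gate and only the calendar is at fault. Item 4 of 7.9.3 covers all of 7.9.2, laboratory items included. Seven days is a minimum, and the dates are declared provisional. Delays of up to five weeks are foreseen in 7.1 and 8.1.2, and 17.2.5 allows later dates for unforeseen reasons. Section 8.1.1 permits extra laboratory tests and places testing on site. A careful PI could read item 4 as needing a result, and could wait for one or obtain one early.

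All of that is true, and it limits the point. But no sentence requires a post-dose laboratory result before escalation. Item 3 asks only for a review of available data, and a statement that no toxicity has occurred can be made when nothing has been measured. The stated grounds for delay do not name awaiting bloods.

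The objection is stronger for 1c than for 1b. Cohort A's results are in hand, and Cohort B's bloods could be drawn and read on site before the injections that day. The consequence is also tempered. Each escalation still needs clinical follow-up of every child, LMM review and DSMB concurrence. In the US adult dose-escalation study (4.5.1) laboratory tests were normal at all three dose levels apart from occasional raised CPK.

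A reader might infer that the laboratory criteria are never usable, or that 50 µg is opened with no laboratory data at all. The documents support neither reading: second doses have bloods 14 days earlier, and 10 µg results precede 1c by 13 days. Nor can one say that a 25 µg laboratory signal would necessarily be seen only after 50 µg had been given, because a same-day result is possible.

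**Conclusion.** The point holds for Doses 1b and 1c, and it should be corrected. If the trial follows 17.2.5, the laboratory criteria in 7.9.2 cannot be applied at either escalation to scheduled post-dose data obtained before the dose day from the cohort just dosed. The gap is clear at 1b, where the blood is one day late and no child has a result. It is narrower at 1c, where the blood falls on the same day and lower-dose results exist. In both cases the DSMB's required concurrence rests on a report dated before the earliest permitted draw.

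This rests on the provisional dates of 17.2.5 and on scheduled tests only. Under Table 9's Day 13, or with an unscheduled test, a Cohort A result could precede 1b, though nothing in the protocol requires one. Laboratory turnaround time is not stated. The exposure is limited to the first injection at the next dose level.

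**What to change.** Add to 7.9.3 that, before Doses 1b and 1c, the Visit 7 CBC, ALT and creatinine results of the cohort just dosed must be available, reviewed by the PI and the LMM, and sent to the DSMB as an addendum to its report.

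To make this workable on the present dose dates, schedule Visit 7 at post-dose Day 11-12 in all three cohorts: Days 11-12 (A), 14 + 11 or 12 = 25-26 (B) and 28 + 11 or 12 = 39-40 (C). This stays inside 14 ± 3. All cohorts should move together because 13.5.2 tabulates antibody levels by dose group at each time point, and moving only A and B would mix dose with sampling time. Align Table 9 with 17.2.5.

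The cost is amendment wording and its approvals, with no extra children, visits or blood. There are two real drawbacks. The first antibody sample comes 2-3 days earlier than nominal Day 14 in every cohort, so its post-dose interval no longer matches Visits 13 and 19. Draws for A and B also fall on a Friday or Saturday before a Monday escalation, which leaves 2-3 days over a weekend for testing, review and the DSMB addendum. On-site testing helps, but turnaround should be confirmed before the dates are fixed.
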